## Abstract

**Background:**

Rehabilitation is seen as crucial in dealing with the demographic change in many European countries. In Germany, for example, after having stayed in a rehabilitation center, patients have the possibility to participate in aftercare programs aimed at promoting long-term health behaviour. Despite the relevance of follow-up support for patients’ long-term health and work ability, participation rates in aftercare programs are quite low. Here, web-based aftercare programs can be a viable alternative to the traditional face-to-face programs due to their flexibility in time and location. This research project aims to use quantitative and qualitative methods to gain more insight into the potential of web-based aftercare programs.

**Methods:**

The goal is to recruit up to 1150 patients at baseline in five rehabilitation centers across Germany. For ethical reasons, partially randomized experimental study design is used to quantitatively assess the effectiveness of web-based aftercare programs. All patients are offered the traditional face-to-face aftercare treatment (IRENA). When patients deny to participate in traditional face-to-face aftercare, they are randomly distributed into either web-based aftercare (digIRENA) or a control group. In all three groups, the SF-12, which measures subjective health, and the WAI, which measures working ability, will be used at baseline, 13 weeks, 26 weeks and 43 weeks after the patients have left the rehabilitation center. BREQ-2, which measures motivation, is used only in the traditional aftercare group and the web-based aftercare group. A multivariate analysis of variance with repeated measurement and latent growth curve models will be used to compare the development of the variables in the three groups. For the qualitative part of the study, interviews with patients and therapists will be conducted to shed light on the applicability, acceptance, and usability of web-based aftercare programs.

**Discussion:**

This study may provide valuable insight into the potential of web-based rehabilitation aftercare programs as a way to supplement traditional face-to-face programs. This seems particularly promising if it can manage to reach those patients who do not currently participate in traditional face-to-face rehabilitation aftercare programs due to time and location constraints.

**Trial registration:**

The trial has been registered at the German Register of Clinical Studies (DRKS) with the registration number: DRKS00022467.

**Supplementary Information:**

The online version contains supplementary material available at 10.1186/s12891-021-04239-z.

## Background

The demographic change in European countries is associated with a shrinking and ageing of the population [1, 2]. These changes are associated with an increase of people receiving a pension, even though there are less people in work who can support this welfare system. This development points towards the importance of promoting actions that aim at improving the health of the working population [3].

One important asset in the promotion of health of the working population is the rehabilitation sector. The aim of rehabilitation is not only to support the recovery process, but also to help patients develop a healthier lifestyle. Studies show that a long-term effect of rehabilitation is difficult to achieve and depends largely on the follow-up support [e.g., [4, 5]]. For instance, in Germany patients have the possibility to participate in an intensive rehabilitation aftercare program after having left the rehabilitation center. Although the costs for this program are covered by the German pension insurance fund, less than 15% of the patients participate in aftercare programs [6]. There are several reasons that may explain this discrepancy between a program that promotes the long-term effects of rehabilitation and the low number of patients that take advantage of this possibility. One main reason is that it is difficult to find time after having returned to work to visit the facilities where aftercare programmes are offered, often during limited time slots. Furthermore, especially in remote areas, the distance between the place of residence and the nearest facility may be too big for regular participation.

The development of technology associated with the increasing possibility of web-based platforms may provide a promising alternative to traditional face-to-face aftercare programs. While new technologies open up possibilities for the entire health care system [7], the term telerehabilitation refers specifically to the delivery of various rehabilitation services via web-based technologies [8]. Web-based rehabilitation aftercare programs could help make health care services more efficient, more accessible and more affordable to larger parts of the population [9]. Irrespective of location and time, patients and therapists can communicate with each other via a web-based platform. The patients do not need to be physically present in the rehabilitation facility and can be supported by supplementary information material via the platform. This flexibility appears to be particularly promising in light of the low number of patients taking part in aftercare programs [10].

Web-based rehabilitation has been shown to be effective in the treatment of cardiovascular diseases [11], neurological applications [12] and in orthopaedic rehabilitation [8, 13]. In addition, empirical evidence suggests that web-based rehabilitation might be a cost-effective tool, compared to traditional rehabilitation [14].

Despite the evidence for clinical and cost effectiveness, web-based rehabilitation is still not widely disseminated [15]. Besides general scepticism about the dangers of the increasing influence of technologies, potentially bringing precarious employment conditions for medical staff [16], another reason may be the lack of studies focusing on more “soft” parameters such as work ability, subjective health, and motivation. The work ability is a result of factors that enable a person to successfully deal with their work demands [17]. A low work ability has been shown to predict the risk of long-term absence at work [18] as well as an early retirement [19]. Subjective health refers to how an individual perceives their own state of health, which might differ from objective health parameters [20]. Longitudinal studies have shown that the subjective health is a predictor of the use of health services [21], and also mortality [22]. Finally, considering the importance of a long-term behaviour change, a plethora of studies highlights that more autonomous types of motivation are associated with the adoption and maintenance of a healthier lifestyle [23].

To conclude, web-based aftercare programs appear to offer a promising alternative to traditional aftercare programs, which may help to ensure the long-term effects of rehabilitation. Using a mix-method design, the purposes of this current study are to assess the efficacy of a web-based platform used in the aftercare of a rehabilitation stay as well as to gain deeper insights into how a web-based platform is perceived by therapists and patients (see Fig. 1).

**Fig. 1 Fig1:**
[figure not shown]
Overview of the aims, criteria, and methods of the digIRENA Study

## Methods

In order to fulfill the purposes of the study, a quantitative and a qualitative study were conducted. An overview of the study is depicted in Fig. 1.

### Quantitative study

In order to examine the effectiveness of the web-based aftercare an intervention study is conducted, comparing a web-based aftercare program with traditional aftercare program and a control condition.

#### Intervention

In this study, two rehabilitation aftercare programs are implemented: the traditional face-to-face aftercare program (IRENA; Intensified Rehabilitation Aftercare) and the web-based aftercare program (digIRENA; digitized Intensified Rehabilitation Aftercare). Both aftercare programs consist of 24 sessions and are tailored to the orthopaedic conditions of the rehabilitants [24]. The program has to be conducted by a qualified physiotherapist who selects the contents of the aftercare program. In the web-based aftercare program, the subjects receive a comparable individualized program with the same number of sessions as the traditional face-to-face IRENA. The web-based program is supervised by an external team of physiotherapists, employed by the provider of the web-based platform. Moreover, the web-based platform provides tools such as relaxation exercises or cooking recipes equivalent to the multimodal approach of a traditional face-to-face aftercare program. In both programs, if patients do not attend a session for at least six subsequent weeks, they are considered dropouts. If inactive, the intervention provider in the web-based aftercare program can encourage the patient to remain in the intervention. Patients in both aftercare groups are continuously supervised by qualified therapists during the interventions. In case of possible harm from the intervention, patients can be referred to appropriate treatment. The participants in the control group receive neither IRENA nor digIRENA. However, they have the possibility to organize their own rehabilitation activities. Finally, all patients can receive additional therapies depending on their health status.

#### Sampling and participants

Patients with orthopedic complaints who have applied for and been approved for rehabilitation on the prescription of a primary care physician are recruited from five rehabilitation centers throughout Germany. The inclusion criteria are that patients are at least 18 years old, have a basic knowledge of the German language, and their primary diagnosis concerns an orthopaedic problem. Furthermore, only patients who are insured with the public pension insurance Knappschaft Bahn See can participate in the study, as the included rehabilitation centres belong to Knappschaft Bahn See. When patients are informed about the possibility to take part in an aftercare program during their stay, they are also asked to participate in the study. In case they give their consent, they are assigned to three groups: (1) traditional face-to-face aftercare program (IRENA), (2) web-based aftercare program (digIRENA), or a control group. For ethical reasons, a partial randomized controlled trial was used. All patients are first asked whether they want to take part in the traditional aftercare program (IRENA). Only if they deny, they are randomly assigned to the web-based aftercare program or the control group. This means that the IRENA condition was offered preferentially and the randomization referred only to the digIRENA and control condition. Sealed envelops are used for the randomization and patients only know their group after opening the envelop. The envelops are distributed with the goal to obtain a ratio of 1:1 between the two groups. Due to nature of the study neither participants nor staff can be blinded to allocation. As an incentive to take part in the study, all patients who complete the study with all measurement occasions receive a 50 Euro Amazon voucher.

Because only a small number of studies exists in relation to web-based aftercare interventions, we chose to take a conservative approach in the power analysis with a small estimated effect size [8]. Conservatively estimating the effect size by Cohen’s *f* = .15, *α* = .05, 1-*β* = .80, with three groups, a correlation among repeated measures of *r* = .30 and a design with three repeated measurement occasions, on average, using an ANOVA with repeated measures (within-between interaction), the calculated total sample size is 573 participants, nearly equally distributed over three groups. Since we expect a dropout rate of about 50% [25], the plan is to recruit 1150 patients.

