#### Data collection of quantitative study

The data collection started in January 2020. Due to the pandemic, the rehabilitation centers did not receive any patients from mid-March until about mid-May. To increase the number of recruited patients, two more rehabilitation centers joined the project in August 2020 (initially there were only three centers). The recruitment of the patients is planned to finish in October 2021. In total, the data collection includes four measurement occasions. The baseline measurement takes place at the rehabilitation center before the start of the intervention, the first follow-up measurement 13 weeks after the baseline, the second follow-up 26 weeks after the baseline, and the third follow-up 43 weeks after the baseline (see Fig. 2). The first three measurement occasions represent the development of the outcome variables, approximately, before, during and at the end of the intervention. Due to the limited duration of the study, the last follow-up measurement is intended to illustrate the sustainability of developments over the next 4 months. For the measurements 2–4, the questionnaires are directly sent to the patients, in accordance to their preference via post or e-mail. A reminder is sent in case the patients have not returned the questionnaires after 2 weeks.

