#### Data analysis of quantitative data

Data are entered by research assistants and checked for accuracy by an independent research assistant. All personal information is pseudo-anonymized. Missing data are treated using either the multiple imputation or the full-information maximum likelihood approach. A first analysis will include all patients who intended to participate in the interventions and a second study will include only those patients who actually completed the interventions. A multivariate analysis of variance with repeated measurements will be used to analyze the data. Additionally, the development of work ability and subjective health will be analyzed by latent growth curve models [32]. These models allow the analysis of linear and nonlinear developments over time. A mediation analysis will be conducted to test whether motivation mediates the effects of the intervention on the attendance rate. The effects of age and gender will be controlled.

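### The stated 80% power and the 573/1150 patients belong to a three-occasion univariate ANOVA, not to the four-occasion repeated-measures MANOVA that is planned

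*Protocol article*

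**What the plan says.** The power paragraph in Methods, Sampling and participants, gives f = .15, α = .05, power .80 and r = .30 for three groups, and "a design with three repeated measurement occasions, on average, using an ANOVA with repeated measures (within-between interaction". The result is 573 patients, nearly equally divided among the groups. With about 50% dropout expected, "the plan is to recruit 1150 patients".

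Data collection of quantitative study states: "In total, the data collection includes four measurement occasions". These are baseline and weeks 13, 26 and 43. The section describes the first three as covering the period before, during and at the end of the intervention, and the fourth as showing sustainability.

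Data analysis of quantitative data states: "A multivariate analysis of variance with repeated measurements will be used to analyze the data". Latent growth curve models are added for work ability and subjective health. Missing data are handled by multiple imputation or FIML. The Abstract names the same MANOVA and the same four time points.

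**The concern.** Two features of the powered test differ from the plan: the number of occasions (three against four) and the test itself (univariate ANOVA against MANOVA). The analysis section lists no univariate repeated-measures ANOVA. A reader therefore cannot take 80% as the power of any analysis the article names.

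The doubling to 1150 also treats every dropout as contributing nothing, whereas multiple imputation and FIML keep the data of patients who miss some waves. A fixed design has a whole number of occasions, so *on average* suggests some allowance that the article does not explain.

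At stake are the claim in the Discussion that the sample can detect even small effects, and a recruitment target for which further clinics and a one-year prolongation were sought.

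**Working it through.** **Inputs.** From the power paragraph: k = 3 groups, m = 3 occasions, r = .30, α = .05, power .80, f = .15. From the data collection section: m = 4. The number of scores tested jointly is not stated. I assume three (WAI, SF-12 physical, SF-12 mental) for illustration.

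**Univariate interaction test.** λ = f²·N·m/(1−r), df1 = (k−1)(m−1), df2 = (N−k)(m−1), noncentral F with sphericity.

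*Step 1: reproduce 573.*
- f = .15, m = 3, N = 127: λ = .0225 × 127 × 3/.70 = 12.25, df 4 and 248, power .803. The printed inputs thus need 127 patients, or 129 in equal groups, not 573.
- Other noncentrality conventions at f = .15 give 271, 268, 533 or 180. None gives 573.
- f = .07, m = 3, N = 571: λ = .0049 × 571 × 3/.70 = 11.99, power .800. Rounded up to equal groups this is 573, where λ = 12.03 and power is .802.
- Dropout step: 573/(1−.50) = 1146, about 1150. This reproduces.

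The remaining steps use f = .07 because it is the value that yields 573. The article does not print it.

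*Step 2: four occasions, one score.*
- N = 573: λ = .0049 × 573 × 4/.70 = 16.04, df 6 and 1710, power .869.
- 80% power needs N = 489 (λ = 13.69, power .800).

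**Multivariate test.** Pillai-type approximation with p scores: q = p(m−1) contrasts, s = 2, df1 = 2q, df2 = s(N−3−q+s). The effect per score is φ = f²·m/(1−r) = .0049 × 4/.70 = .028. With one canonical root, V = φ/(1+φ) and λ* = N·s·V/(s−V).

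*Step 3: one score, multivariate approach (q = 3), N = 573.* V = .028/1.028 = .0272, λ* = 573 × 2 × .0272/1.9728 = 15.82, df 6 and 1138, power .863. 80% needs 497, or 498 in equal groups.

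*Step 4: three scores jointly (q = 9, df 18 and 1126), N = 573.*

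| Pattern of effect | Noncentrality | Power |
|---|---|---|
| One score responds, scores uncorrelated | 15.82 (16.04 if λ is used directly) | .659 (.667) |
| All three respond equally, scores correlated .3 | 16.04 × 3/1.6 = 30.08 | .951 |
| All three respond equally, scores uncorrelated | 46.19 (φ = .084) | .997 |

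In the first row, 80% power needs 737 complete patients, or 738 in equal groups.

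*Step 5: the same at the printed f = .15.* The least favourable row of step 4 needs 175 (177 in equal groups), and 573 gives more than 99.9%. The possible shortfall therefore exists only at the smaller effect size.

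**Dropout.** If 573 already allowed in full for missed waves, up to 1150 − 573 = 577 of the recruited patients would be surplus to the calculation. If it did not, none would be on that account. The article does not say which applies.

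**The case against.** The strongest reply is that nothing here shows lost power. Planning on three occasions is the cautious choice, since adding a fourth lowers the requirement for one score from 573 to 489. The data collection section also gives a reason to concentrate on the first three occasions. Entering each score separately by the multivariate approach needs only 498. A joint test can do better or worse than 80%, and the number of scores in it is a detail that a condensed article may leave to the full plan. All of this stands, and it is why the point is a mismatch and not a demonstrated power deficit.

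A reader might go further and infer that *on average* can only mean patients supplying three of four waves, so that dropout is counted twice. A linear loss to 50% over four waves does give 1 + 5/6 + 4/6 + 1/2 = 3.0. But that pattern is an assumption found nowhere in the article, and other readings exist. The three occasions could be those spanning the intervention, or those of attendance, which is not measured at baseline. Neither explains the words well: each is exactly three, and attendance is recorded in only two groups. Still, they prevent the inference from being forced.

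The Intervention section, moreover, defines dropouts by missed sessions over at least six weeks, not by missing questionnaires. If the 50% refers to programme dropout, the doubling may be meant to protect the planned second analysis of patients who completed the intervention. Double counting therefore remains a possibility to be cleared up.

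What the reply does not remove is that the article states a test, a number of occasions, an N and a power, and that the first two disagree with its own design and analysis sections.

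**Conclusion.** The point holds as an inconsistency. The 80% power, the 573 and the 1150 were computed for a test and a number of occasions that differ from those planned. At f = .07 and r = .30, with 573 complete patients in equal groups, power for the four-occasion analysis is about .86 to .87 for a single score. For three scores jointly it runs from about 66–67% to above 99%, depending on how many scores respond and how they correlate.

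These figures rest on an effect size that the article does not print and on an assumed set of three scores. At the printed f = .15 every variant is amply powered, and the trouble is instead that 573 does not follow from the stated inputs.

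The documents do not support a statement that the trial is underpowered, nor that 1150 is proven to be too many.

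**What to change.** 1. Name the single test that is powered. Either state which scores enter the MANOVA and power that test, or change the analysis section to the univariate ANOVA that was powered.
2. Rerun the calculation with four occasions, or say explicitly that the powered contrast uses only the first three. Report the effect size actually used, so that the printed f and the 573 agree.
3. Define *on average*, and say whether the 50% is loss of questionnaires or dropout from the programme. Count loss once, in a way consistent with multiple imputation or FIML.
4. Restate either the N needed or the power delivered at 1150.

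The cost is one rerun and a few corrected sentences, with no additional patients. If the chosen test is a joint one in which only one score is expected to respond, the calculation would ask for 738 complete patients, or 738/.50 = 1476 recruited by the article's own inflation. In that case the honest course is to report the lower power at 1150, or to power a single-score test, and not to retain the 80%.

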## Discussion

The purposes of this study are 1) to assess the efficacy of a web-based platform used in the aftercare of a rehabilitation stay whilst looking at 1a) attendance, 1b) work ability, 1c) subjective health and 1d) motivation as well as 2) to gain deeper insights into how a web-based platform is perceived by therapists and patients whilst looking at 2a) applicability, 2b) acceptance and 2c) usability.

Due to an increased proportion of aging population in Germany, web-based rehabilitation aftercare could be an effective supplement to the traditional face-to-face rehabilitation aftercare. It has the potential to reach those people who cannot easily reach and not have access to traditional face-to-face rehabilitation aftercare. As traditional face-to-face rehabilitation aftercare suffers from low level of usage due to inflexible offers in terms of time and long distances to rehabilitation centers, web-based aftercare could help tackle some of these problems.

This study has several strengths and limitations. A strength of this study is the design as a partially randomized control trial, which enables us to draw strong conclusions about the effectiveness of the intervention. Additionally, the intended sample of the study is large enough to find even small effects. Furthermore, the longitudinal structure of the study enables us to examine development trajectories in the outcome variables. Finally, we use reliable and valid measures of the outcome variables, which have been tested in a vast amount of studies.

A limitation is that the corona pandemic partially interrupted the course of the study so that we lost a part of the participants due to this interruption. Therefore, we requested to include additional clinics and to prolong the duration of the study to reach the aimed number of participants. It is possible that the interruption could influence the results of the study.

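### The power paragraph is internally inconsistent: its stated inputs, including f = .15, give about 129 patients under the standard calculation, not the stated 573

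*Protocol article*

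**What the plan says.** The section Sampling and participants contains the article's only sample-size justification. It introduces the effect size with the words "we chose to take a conservative approach in the power analysis with a small estimated effect size", sets f = .15, alpha = .05 and power = .80 for three groups, and adds "a correlation among repeated measures of *r* = .30 and a design with three repeated measurement occasions, on average". The test and the result are then given together: "using an ANOVA with repeated measures (within-between interaction), the calculated total sample size is 573 participants", split almost evenly over the three groups. An expected dropout of about 50% then leads to a recruitment target of 1150.

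Two other places bear on the point. Data collection of quantitative study says "In total, the data collection includes four measurement occasions". The Discussion lists as a strength that "the intended sample of the study is large enough to find even small effects".

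**The concern.** The paragraph gives nearly everything needed to repeat the calculation; only the effect-size convention and the sphericity correction (epsilon) are unstated. A sample of 573 looks far too large for f = .15 with three repeated measures per patient, so either the effect size or the sample size appears to be misprinted or to come from a different calculation.

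The recruitment target is built on 573. The planning effect is also what readers will use to judge a null result: they would ask whether the trial could have seen an effect of the planned size, and at present they cannot tell what that size was.

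**Working it through.** **Inputs** (Sampling and participants): f = .15, alpha = .05, power = .80, k = 3 groups, m = 3 occasions, r = .30, omnibus interaction F test. Epsilon is not stated. I take 1 and use the lower bound 1/(m − 1) = 0.5 as the other end of the range.

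**Formula.** For the within-between interaction, λ = f² · N · m · ε / (1 − r), with df1 = (k − 1)(m − 1)ε and df2 = (N − k)(m − 1)ε. Power is the probability that a noncentral F with these parameters exceeds the central 5% critical value. N is the smallest multiple of 3 with power of at least .80.

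**1. The plan's own figure.** At N = 573 and ε = 1, λ = .0225 × 573 × 3 / .70 = 55.25, with df 4 and 1140. Power is above .9999, so 573 is not the 80% solution.

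**2. What the stated inputs require.** At N = 129, λ = .0225 × 129 × 3 / .70 = 12.44, with df 4 and 252, and power is .810. At N = 126 it is .799. The answer is therefore 129, and 573/129 = 4.4.

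**3. Can an unstated choice explain the gap?** With f, alpha, power, k and m as stated:

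| Convention | N at ε = 1 | N at ε = 0.5 | Power at N = 573 (ε = 1; ε = 0.5) |
|---|---|---|---|
| λ = f²Nmε/(1 − r) | 129 | 204 | > .9999; .998 |
| λ = f²N(m − 1)ε, no correlation term | 270 | 432 | .991; .904 |
| λ = f²(N − k)(m − 1)ε, no correlation term | 273 | 435 | .991; .902 |

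Other tests at f = .15 do not reach 573 either: multivariate test 270, between-groups effect 234, within effect 102, one-way ANOVA 432. Nor do other inputs to the standard formula: two occasions 153, four occasions 111, r = 0 gives 180. A few settings come close (for example 567 to 570), but they need the stated alpha or power to change as well.

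**4. Which single change restores 573?** Put f = .07 and leave everything else as stated: λ = .0049 × 573 × 3 / .70 = 12.03, with df 4 and 1140, and power is .802. N = 570 gives .799, so 573 is the exact solution for equal groups. The neighbours do not fit: f = .069 gives 588 and f = .071 gives 555. Under a convention without the correlation term, 573 would instead correspond to f of about .10.

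**5. Dropout step.** 573/(1 − .50) = 1146, rounded to 1150. This is correct. The same step from 129 would give 258.

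**The case against.** The best defence is that the discrepancy runs in the safe direction. A sample of 573 exceeds the requirement for f = .15 under every convention tried, the dropout arithmetic is right, and no patient number has to change. That stands, and it limits the consequence. It does not make the sentence correct: a calculated sample size should follow from its inputs, and an unseen analysis plan cannot make both figures true.

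A reader might infer more than the article supports:

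- **That f was certainly misreported about two-fold (.15/.07 = 2.1).** The exact match at f = .07 is strong evidence, but the article never mentions .07 and does not name its convention. Under another convention the matching value is about .10.
- **That the Discussion's statement about small effects is false.** The article measures smallness on the f scale and calls .15 small. At N = 573 the standard calculation gives power .988 at f = .10 and above .9999 at f = .15. A benchmark in SD units could give a different answer, but the article sets none.
- **That planning on three occasions is an error because four are collected.** The text says three on average, and the fourth occasion is described as showing sustainability after the intervention. Four occasions would need fewer patients (489 instead of 573 at f = .07; 111 instead of 129 at f = .15), so using three is conservative.

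**Conclusion.** The stated effect size and the stated sample size cannot both be right. On the standard calculation with ε = 1, the stated inputs need 129 patients and 573 is 4.4 times that number. The least favourable combination of unstated choices examined raises the requirement to about 435, still well short of 573. The most economical explanation is that the calculation was run at f = .07, but this is an inference that only the original calculation can confirm.

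This is an error in the reported justification, not a shortage of patients. The trial is not underpowered for f = .15. Power at 573 would be above 99.9% on the standard calculation and about 90% on the least favourable combination, in both cases more than the stated 80%. The practical harm is to interpretation, because the planning effect could be out by a factor of about two.

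**What to change.** Retrieve the original calculation, then correct Sampling and participants in one of two ways:

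1. If 573 came from a smaller effect, restate f so that it agrees with 573 (f = .07 if that is what was run).
2. If f = .15 was truly intended, state the power that 573 delivers (above 99.9% on the standard calculation) and give the separate reason for keeping 573 and 1150. Simply replacing 573 with 129 would not do, because it implies about 258 recruits and removes the stated basis for 1150.

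In either case, name the effect-size convention and the value of epsilon. Give the corrected detectable effect wherever the text describes the planning effect, including the Discussion's remark on small effects, so that a null result is read against the right figure.

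The cost is a check of the original calculation and a few sentences of text. No change to recruitment is needed.

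### The sample size assumes three nearly equal groups, but patient choice sets the IRENA group size and the only uptake figure quoted points to an unequal split

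*Protocol article*

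**What the plan says.** The power analysis in Methods, Sampling and participants, uses "Cohen’s *f* = .15, *α* = .05, 1-*β* = .80, with three groups", together with an assumed within-patient correlation of 0.30 between occasions and "a design with three repeated measurement occasions, on average". The test that it powers is the within-between interaction of a repeated-measures ANOVA. The result is "573 participants, nearly equally distributed over three groups", doubled for an expected dropout of about 50% to a recruitment target of 1150.

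The allocation rule stands in the same section. Every patient is offered IRENA before anything else. "Only if they deny, they are randomly assigned to the web-based aftercare program or the control group". The 1:1 goal for the envelopes applies to those two groups only.

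The only figure on uptake is in the Background: "less than 15% of the patients participate in aftercare programs". The Discussion then claims that the planned sample suffices for even small effects.

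**The concern.** Near-equal group sizes are stated as part of the sample-size result, but nothing in the allocation rule produces them. Randomisation balances digIRENA against control. The size of IRENA relative to both is whatever patients choose. The target is set on total enrolment, so 1150 can be reached with very different numbers in the three groups.

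Two things are at stake. If few patients choose IRENA, the comparison of web-based with traditional aftercare, which is a stated aim, has less precision than equal thirds imply. If many choose it, the randomised comparison of digIRENA with control shrinks although the enrolment target is met. In either case the stated 80% omnibus power belongs to a split that may not occur.

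**Working it through.** **Inputs from the article.** f = 0.15, α = 0.05, power 0.80, k = 3 groups, m = 3 occasions, r = 0.30, N = 573 analysed, 50% dropout, 1150 recruited (Sampling and participants); uptake under 15% (Background).

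**Assumptions added here.** IRENA uptake u among enrolled patients, taken over a range; equal dropout in all groups; a standardised difference d for pairwise contrasts, which the article does not give.

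**1. The plan's own figure.** The inflation reproduces: 573 / (1 − 0.50) = 1146, rounded to 1150. The figure of 573 does not. With df1 = (k − 1)(m − 1) = 4, df2 = (N − k)(m − 1) = 2(N − 3) and sphericity, the required N depends on the noncentrality convention:

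| Noncentrality | Required N |
|---|---|
| f²·N·m/(1 − r) | 127 |
| f²·N·(m − 1) | 268 |
| f²·N/(1 − r) | 374 |
| f²·N | 533 |

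This is a separate matter. Below, 573 is taken as the sponsor's figure and all power is relative to 80% at equal thirds.

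**2. The split.** IRENA = u·N; digIRENA = control = (1 − u)·N/2. Equal thirds require u = (1 − u)/2, so u = 1/3, more than twice 15%. At u = 0.15:
- Analysed: 0.15 × 573 = 86 and 0.85 × 573/2 = 243.5, so about 86/244/244 instead of 191/191/191.
- Recruited: 0.15 × 1150 = 172.5 and 0.85 × 1150/2 = 488.75, so about 173/489/489.

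**3. Pairwise contrasts.** Two-sample comparison, two-sided 5%, with d = 0.287, the difference that gives 80% power at 191 versus 191. The noncentrality is d·√(n₁n₂/(n₁ + n₂)). At 15% uptake this is 0.287 × √(243.5/2) = 3.17 for digIRENA versus control, and 0.287 × √(86 × 243.5/329.5) = 2.29 for IRENA versus digIRENA.

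| IRENA uptake | Analysed (IRENA / each randomised group) | Power, digIRENA vs control | Power, IRENA vs either other group |
|---|---|---|---|
| 10% | 57 / 258 | 90% | 50% |
| 15% | 86 / 244 | 89% | 63% |
| 20% | 115 / 229 | 87% | 71% |
| 33.3% | 191 / 191 | 80% | 80% |
| 50% | 287 / 143 | 68% | 80% |
| 60% | 344 / 115 | 58% | 76% |

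The differences detectable with 80% power at 15% uptake are about 0.25 for the randomised contrast and 0.35 for the IRENA contrasts, against 0.287 for all at equal thirds. With d = 0.30 the pattern is the same: 91% and 66% at 15% uptake, 83% for both at equal thirds, and 72% and 62% for the randomised contrast at 50% and 60% uptake.

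**4. The omnibus test.** At N = 573, 80% power corresponds to a noncentrality of 11.985. This scales with the variance of the group effects weighted by group share:
- Only IRENA differs: (0.15 × 0.85)/(1/3 × 2/3) = 0.574; noncentrality 6.88; power 53%.
- IRENA, digIRENA and control in equal steps, in that order: ratio 0.749; power 66%.
- Only control, or only digIRENA, differs: ratio 1.100; power 84%.
- IRENA midway between the other two: 0.85/(2/3) = 1.275; noncentrality 15.28; power 90%.

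**The case against.** The case on the other side is substantial, and several stronger readings that a reader might infer do not survive it.

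- **That the uptake figure makes equal thirds impossible.** It does not. It is a general rate for rehabilitation patients in Germany. The enrolled patients are orthopaedic, have one insurer, come from its own centres, consented to an aftercare study and are offered a voucher. Their uptake may be lower or higher. The figure leaves equal thirds unsupported, not excluded.
- **That the article misstates the power of each comparison.** It states no pairwise power, only 80% for one omnibus interaction test. That test can gain or lose power from the imbalance.
- **That the randomised comparison is underpowered.** On the article's only uptake figure it gains, from 80% to about 89%. The loss falls on the IRENA contrasts, which self-selection limits as well as size. The randomised contrast suffers only if uptake exceeds one third, and no figure in the article points there.

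It can also be said that the pairwise percentages come from a simple two-group comparison, not from the planned repeated-measures model. That stands: they show direction and rough size and do not measure the planned test. Finally, this is a condensed article whose design figure is not shown, so the absence of pairwise power or an uptake table is not in itself a fault. What remains is a statement that the article does make, about near-equal groups, which its own allocation rule does not deliver.

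**Conclusion.** The point holds as an unsupported design assumption. The sample-size result rests on near-equal groups, patient choice determines the IRENA share, no expected share or balancing rule accompanies it, and the only uptake figure quoted is less than half of what equal thirds need. At 15% uptake, relative to 80% at equal thirds, the randomised contrast gains about 9 percentage points, the IRENA contrasts lose about 17, and omnibus power lies between about 53% and 90%. At 50% to 60% uptake the randomised contrast loses about 12 to 22 points.

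These sizes rest on the assumed uptake, on equal dropout across groups, on d of about 0.287 and on taking 573 as given. The imbalance itself depends only on uptake and on dropout by group, and would arise at any total.

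**What to change.** In Sampling and participants, delete the wording on near-equal distribution and state the IRENA share expected among consenting patients, with its basis. At the planned 1150, restate power or detectable difference for the omnibus test, for digIRENA versus control and for the IRENA contrasts, over a range of uptake such as 10% to 60%. Qualify the Discussion's claim about small effects accordingly.

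Monitor the number randomised as recruitment proceeds and keep the total of 1150. A stopping point set on the randomised patients alone (2 × 191 = 382 analysed, 382/0.50 = 764 randomised) should not replace it. At 15% uptake it would be reached at about 764/0.85 = 899 patients, with about 135 in IRENA and 67 of them analysed. With d = 0.30, power would then be 83% for the randomised contrast and 56% for IRENA versus digIRENA, both below the 91% and 66% that 1150 gives.

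The cost is rewording, a short recalculation and a running count. The downside is that the stated power becomes less favourable for some contrasts.
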